**Metformin eligibility criteria**
*Inclusion criteria*
1. No diagnosed diabetes or known contraindications to metformin treatment.^c^
2. Elevated adiposity (BMI ≥ 25 kg/m^2^ OR waist circumference > 102 cm in men and > 88 cm in women) OR mildly impaired fasting glucose (6.1–6.9 mmol/l).^d^
*Exclusion criteria*
1. Use of metformin for any indication
2. History of intolerance to metformin used for any indication
3. Diabetes diagnosed or suspected at baseline (e.g. HbA1c ≥ 6.5%^d^, fasting glucose ≥ 7 mmol/l^d^, or 2HPG ≥ 11.1 mmol/l)
4. Hypersensitivity to metformin or to any of the excipients or placebo compounds
5. Metformin contraindications, e.g. hepatic insufficiency and severe renal failure. Individuals with history/presence of known renal or liver disease, congestive heart failure, alcohol abuse, calculated GFR < 60 ml/min^d^ will also be excluded from the study
6. Any type of acute metabolic acidosis (such as lactic acidosis, diabetic ketoacidosis)
7. Acute conditions with the potential to alter renal function such as dehydration, severe infection, and shock
8. Disease which may cause tissue hypoxia (especially acute disease or worsening of chronic disease) such as decompensated heart failure, respiratory failure, recent myocardial infarction, and shock
9. Women of childbearing potential

*2HPG *2-h plasma glucose, *AD *Alzheimer’s disease, *BMI *body mass index, *CAIDE *Cardiovascular Risk Factors, Aging and Dementia, *CERAD *Consortium to Establish a Registry for Alzheimer’s Disease, *GFR* glomerular filtration rate, *HbA1c *haemoglobin A1c, *MoCA *Montreal Cognitive Assessment

^a^MoCA was chosen over MMSE due to its higher sensitivity to subtle and early cognitive changes in older adults without dementia (Markwick, J Clin Exp Neuropsychol, 2012). The cut-offs were chosen to more accurately select a target population that excludes both high performers and people with substantial impairment including dementia

^b^Individually assessed by the study physician. Clinical assessment will provide a more accurate overall picture of the participant’s cognitive and functional level. If the need for memory clinic referral for further evaluation is identified based on clinical judgment, participants will be excluded irrespective of their MoCA or CERAD scores

^c^The process to determine eligibility for Metformin starts after the Randomisation 1 (Fig. 2) and it is structured in specific steps to minimise participant burden. The first step covers eligibility criteria assessed through baseline data (e.g. BMI, waist circumference, fasting glucose, diagnosis of diabetes, and relevant medical history). The second step is an additional screening visit in step-1 eligible participants (remaining eligibility and safety criteria, minus OGTT). Finally, OGTT is conducted in step 2 eligible participants

^d^Assessed with baseline visit data

Dates for the Completion of Enrolment (last participant, Randomisation 1; Fig. 2); Study Completion (last participant last visit); and Primary Analysis (primary publication ready for submission) are currently estimated to be February 2025; February 2027; and September 2029, respectively.

### Data collection

Participants will be invited to a first screening visit, where basic demographics will be collected, and Study Eligibility Criteria (Table 1) will be assessed. Eligible participants will be invited to the baseline visit, where all outcome measures will be assessed prior to the first randomisation step (FINGER 2.0 intervention or SMGI). Participants randomised to the FINGER 2.0 group will start receiving the SMLI and will be further assessed for the Metformin Eligibility Criteria using baseline data and additional assessments at a second screening visit where metformin eligibility assessments will be completed (Table 1). Eligible participants will undergo the second randomisation step, and treatment will be initiated.

All participants will be invited to three additional outcome assessments, where basic safety assessments will be also conducted. At 6 months, a subset of outcomes related to blood sample collection, physical measurements, and health status will be assessed. At 12 and 24 months (end of study) a full outcomes assessment will be conducted, with additional data collection on trial participation adherence and feedback.

Participants randomised to the metformin/placebo treatment will undergo additional safety assessments, every 2 weeks until the full dose is established, and every 3 months after that.

Nominating a study partner to provide information for the assessment of the Clinical Dementia Rating scale Sum of Boxes (CDR-SB) [23] will be supported, but not mandatory.

### Outcomes

Primary and secondary outcomes comparison will be conducted on the FINGER 2.0 multimodal intervention group (active arm) vs the SGMI group (control arm). A comparison of exploratory outcomes will be conducted among the three SMLI + metformin/placebo groups.

Table 2 presents the schedule of the outcomes’ assessment. The bibliography for validated assessment tools, tests, and scales used in the trial is presented in Supplementary Table 1.

**Table 2 Tab2:** Full schedule of outcomes assessments

Assessments	Outcomes assessment visits			
***Primary and secondary outcomes***	**Baseline**	**6 months**	**12 months**	**24 months**
Neuropsychological Test Battery (Primary outcome and secondary cognitive outcomes)	**X**		**X**	**X**
Clinical Dementia Rating Sum of Boxes (Study Partner required)	**X**		**X**	**X**
Activities of daily living	**X**		**X**	**X**
Healthy Lifestyle Index	**X**		**X**	**X**
Physical measurements (BMI, waist, waist/hip ratio, blood pressure)	**X**	**X**	**X**	**X**
Blood markers (lipid profile and glucose metabolism)	**X**	**X**	**X**	**X**
OGTT (only groups receiving metformin/placebo)	**X**		**X**	**X**
Incident cardiovascular disease	**X**		**X**	**X**
FINGER healthy diet index, nutrient and food intake	**X**		**X**	**X**
Levels of physical activity (self-reported and objectively measured)	**X**		**X**	**X**
Short Physical Performance Battery	**X**			**X**
Hand grip strength, and timed 10-m dual-task test	**X**		**X**	**X**
Center for Epidemiological Studies-Depression Scale	**X**		**X**	**X**
Perceived Stress Scale	**X**		**X**	**X**
Insomnia Severity Index	**X**		**X**	**X**
RAND36 and 15D scales for health-related quality of life	**X**		**X**	**X**
Self-reported data for utilisation of healthcare resources	**X**		**X**	**X**
***Exploratory outcomes***				
Healthy lifestyle changes, e.g. exercise, diet, cardiovascular/metabolic factors and biomarkers, and cognitive activity	**X**		**X**	**X**
AD-related blood biomarkers	**X**	**X**	**X**	**X**
Neuroimaging (Planning phase)	**X**			**X**
Retention rate	Continuously during the study			
Adherence to the SMLI and its individual components	Continuously during the study based on participation to the SMLI structured activities			
Target metformin dose	Continuously during the study with compliance to treatment assessed at each dispensing appointment (every 3 months)			

The bibliography for assessment tools, tests, and scales used in the trial is presented in Supplementary Table 1

*AD* Alzheimer’s disease, *BMI* body mass index, *FINGER* Finnish Geriatric Intervention Study to Prevent Cognitive Impairment and Disability, *OGTT* oral glucose tolerance test, *SMLI* Structured Multimodal Lifestyle Intervention

#### Primary

Change in global cognition measured through a “Composite Neuropsychological Test Battery (NTB) Overall Score” modified from the FINGER trial [24] to ensure the availability of all tests in the trial languages (Table 3) is the trial primary outcome. The 14 test components will be first standardised to their baseline mean and standard deviation. Then, “composite cognitive domain scores” will be calculated by averaging the individual *z*-scores of the components that are relevant for each cognitive domain (memory, executive function, and processing speed). Finally, the composite NTB overall score will be obtained as the average of the composite cognitive domain scores. Composite cognitive domain scores will be calculated if results for at least 3/5 (executive function); 2/3 (processing speed); and 3/6 (memory) tests are available.

**Table 3 Tab3:** Tests and scores included in the Neuropsychological Test Battery conducted for Primary/Cognitive outcomes assessment

Cognitive test	Item/score included	Relevant cognitive domain
WMSR—Logical Memory	Immediate recall	Memory
WMSR—Logical Memory	Delayed recall	Memory
WMSR—Visual Paired Associates	Immediate recall	Memory
WMSR—Visual Paired Associates	Delayed recall	Memory
HVLT	Learning score	Memory
HVLT	Delayed recall score	Memory
Digit Span	Maximum correct span	Executive functioning
CERAD Category Fluency	Number of correct animals mentioned	Executive functioning
Category Fluency II	Number of correct fruits/vegetables mentioned	Executive functioning
TMT	Score A	Processing speed
TMT	Shifting score B-A	Executive functioning
Stroop	Condition 2	Processing speed
Stroop	Interference score condition 3 -2	Executive functioning
WAIS-DSST	Total score	Processing speed

The bibliography for assessment tools, tests, and scales used in the trial is presented in Supplementary Table 1

*CERAD *Consortium to Establish a Registry for Alzheimer’s Disease, *DSST *Digit-Symbol Substitution Test, *HVLT *Hopkins Verbal Learning Test, *TMT *Trail Making Test, *WAIS *Wechsler Adult Intelligence Scale, *WMSR *Wechsler Memory Scale Revised

#### Secondary

Change in the following secondary endpoints will be included: Composite cognitive domain scores (memory, executive function, processing speed); CDR-SB (only if a study partner is interviewed), and Instrumental Activities of Daily Living; Healthy Lifestyle Index, a composite score based on exercise, diet, lifestyle cardiovascular risk factors, and social and cognitive activity; BMI, waist, waist/hip ratio, blood pressure, lipid profile and glucose metabolism, including OGTT for participants randomised to the metformin/placebo treatment; incident cardiovascular disease; FINGER healthy diet index, nutrients and food intake; Self-reported and objectively measured (with Actigraph) levels of physical activity; Short Physical Performance Battery, hand grip strength, and timed 10-m dual-task test; Center for Epidemiological Studies-Depression Scale; Perceived Stress Scale; Insomnia Severity Index; RAND36 and 15D scales for health-related quality of life; Self-reported data for utilisation of healthcare resources.

#### Exploratory (SMLI + metformin/placebo groups)

(i)Between-group differences in healthy lifestyle changes, e.g. exercise, diet, cardiovascular/metabolic factors and related biomarkers, and cognitive activity(ii)AD-related blood biomarkers (e.g. amyloid, tau, neurofilament light polypeptide); a neuroimaging sub-study is currently planned(iii)Retention rate, and adherence to the SMLI, its individual components, and target metformin dose

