**Methods:**

MET-FINGER is an international randomised, controlled, parallel-group, phase-IIb proof-of-concept clinical trial, where metformin is included through a trial-within-trial design. 600 participants will be recruited at three sites (UK, Finland, Sweden). Participants at increased risk of dementia based on vascular risk factors and cognitive screening, will be first randomised to the FINGER 2.0 intervention (lifestyle + metformin if eligible; active arm) or to receive regular health advice (control arm). Participants allocated to the FINGER 2.0 intervention group at risk indicators of T2D will be additionally randomised to receive metformin (2000 mg/day or 1000 mg/day) or placebo. The study duration is 2 years. The changes in global cognition (primary outcome, using a Neuropsychological Test Battery), memory, executive function, and processing speed cognitive domains; functional status; lifestyle, vascular, metabolic, and other dementia-related risk factors (secondary outcomes), will be compared between the FINGER 2.0 intervention and the control arm. The feasibility, potential interaction (between-groups differences in healthy lifestyle changes), and disease-modifying effects of the lifestyle-metformin combination will be exploratory outcomes.

The lifestyle intervention is adapted from the original FINGER trial (diet, physical activity, cognitive training, monitoring of cardiovascular/metabolic risk factors, social interaction) to be consistently delivered in three countries. Metformin is administered as Glucophage®XR/SR 500, (500 mg oral tablets). The metformin/placebo treatment will be double blinded.

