**Fig. 1 Fig1:**
[figure not shown]
Summary of the mechanisms linking type 2 diabetes (T2D) and its risk factors to dementia/AD and possible metformin targets (Modified from Yarchoan M and Arnold SE, Diabetes, 2014)

The MET-FINGER study aims to test a FINGER 2.0 multimodal intervention (active arm), combining a Structured Multimodal Lifestyle Intervention (SMLI, based on the original FINGER model) with metformin (where appropriate) in a *APOE* ε4-enriched population of older adults at-risk for dementia, against a Self-Guided Multimodal Intervention (SGMI, general health advice; control arm).

The primary objective is to test the effect of the FINGER 2.0 intervention versus the SGMI on change in global cognition. Secondary objectives are to test the effect of the FINGER 2.0 intervention versus the SGMI on change in individual cognitive domains, functional status, and lifestyle, vascular, metabolic and other dementia-related risk factors. Exploratory objectives will investigate, within the SMLI-metformin combination groups, (i) potential interactions between metformin and lifestyle changes; (ii) potential disease-modifying effects of the lifestyle-metformin combination; and (iii) feasibility of the metformin + lifestyle combination; in the context of prevention of cognitive impairment.

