## Methods

### Study design

MET-FINGER is a randomised, controlled, parallel-group, multicentre phase-IIb proof-of-concept clinical trial testing the FINGER 2.0 multimodal lifestyle-based intervention, including a pharmacological trial-within-trial with metformin (Fig. 2). The participants will be first randomised 1:1 to the FINGER 2.0 intervention (SMLI for all participants + metformin where appropriate; active arm) or the SGMI (regular health advice; control arm). Participants allocated to the FINGER 2.0 intervention, and with indicators T2D risk, but no diagnosed/suspected diabetes, will be randomised 1:1:1 to receive metformin 2000 mg/day, metformin 1000 mg/day, or placebo, together with the SMLI. Participants allocated to the FINGER 2.0 intervention but not eligible for metformin treatment will receive the SMLI alone. At each site, both randomisation steps (Fig. 2) are carried out using a computer-generated list from the OpenClinica database. In each randomisation step, the list is stratified by site and programmed using random blocks of various sizes.

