For most exploratory outcomes of the lifestyle + metformin trial-within-trial, the same model in the primary analysis of the trial will be used for continuous outcome variables; for categorical outcome variables (e.g. adherence-related outcomes) logistic regression models will be applied. For retention rate and target metformin dose, chi-2 test will be used to compare the three arms.

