#### Metformin/placebo treatment

The study-drug treatment will be conducted double-blinded. All participants receiving the SMLI (*n* ~ 300) who are eligible for metformin treatment (Table 1; estimated rate based on data from recruitment sources = 50%, unpublished) will be randomised to either: metformin 2000 mg/day, metformin 1000 mg/day, or placebo.

Metformin will be administered as Glucophage®XR 500 (“SR” in the UK), in form of 500 mg oral tablets. The placebo is prepared based on Glucophage® SR/XR specifications. The placebo will be manufactured to be identical to the active tablets. Both metformin and placebo will be manufactured in bulk by Merck KGaA (Darmstadt, Germany) and prepared at Guy’s and St Thomas’ NHS Foundation Trust Pharmacy Manufacturing Unit (London, UK) in identical dispensing packs, containing sufficient tablets for 3 months. To obtain the target dose, a blinded system will be in place to allow participants to take four tablets/day as follows:2000 mg/day 4 × Glucophage® SR/XR 5001000 mg/day 2 × Glucophage® SR/XR 500 + 2 × placeboPlacebo 4 × placebo

Participants are recommended to take all four daily tablets together with the evening meal. Gastrointestinal disorders are the most common adverse events; the extended-release formulation will be used to decrease such risks. Additionally, since these undesirable effects occur most frequently during therapy initiation, resolve spontaneously in most cases, and can be reduced by gradual dose increase, the study drug will be titrated from one tablet/day adding one tablet/day each week until the target dose is reached. If the target dose cannot be achieved, participants will be first instructed to reduce the dose to two tablets/day (half-dose) and if the half-dose cannot be achieved, the study-drug treatment will be discontinued.

Based on the safety profile of metformin, the treatment will be discontinued if it is deemed unsafe for the participant due to an adverse event/serious adverse event associated with the treatment (e.g. anaphylaxis, vitamin B12 deficiency); any severe adverse event considered to be related to the study treatment is reported; signs of hypersensitivity are reported; the participant develops diabetes; eGFR < 60 mL/min.

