The choice of metformin as a plausible and promising pharmacological treatment to combine with the SMLI was based on the well-established link between T2D and dementia/AD, and evidence of its relevance for AD/dementia prevention [18–20]. Metformin crosses the blood–brain barrier in animal models as well as humans, [37] activates AMPK in CNS tissue; ameliorates brain insulin resistance; and reduces AD pathology in preclinical models [18]. It showed beneficial effects on several risk factors for dementia/AD, e.g. peripheral insulin resistance, T2D, metabolic syndrome, elevated adiposity, and cardiovascular factors [19]. Metformin was also shown to counteract mechanisms of senescence, [38–40] which is increased in AD and other neurodegenerative disorders, [21] independently of its anti-diabetic action [41]. A beneficial association between metformin (compared with sulfonylureas or non-users) and dementia risk was also reported in large observational studies [42, 43]. Recently, a large (*n* = 210,000 +) cohort study reported that, in patients with T2D, metformin treatment was significantly associated with lower dementia risk compared with no treatment [44]. Only few RCTs (in individuals with MCI) have so far been conducted testing metformin in the context of dementia/AD with promising results on cognition and neuroimaging, [37, 45] and one RCT is currently ongoing (ClinicalTrials.gov NCT04098666), but the combination of metformin and healthy lifestyle changes has never been tested for dementia/AD prevention.

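### Exploratory objective (i) would read metformin's own effect on cardiometabolic factors as a lifestyle change or a metformin-lifestyle interaction

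*Protocol article*

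**What the plan says.** The objectives at the end of the Background give the first exploratory aim, within the groups that combine the SMLI with study drug, as "potential interactions between metformin and lifestyle changes". The Methods part of the abstract says how this is to be read: "potential interaction (between-groups differences in healthy lifestyle changes". A difference between groups in the outcome is thus the evidence of interaction.

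The outcome is defined in two places with the same content. The exploratory outcomes section has "Between-group differences in healthy lifestyle changes, e.g. exercise, diet, cardiovascular/metabolic factors and related biomarkers, and cognitive activity", and the exploratory block of Table 2 has "Healthy lifestyle changes, e.g. exercise, diet, cardiovascular/metabolic factors and biomarkers, and cognitive activity". Both put cardiometabolic factors and biomarkers under the same label as exercise, diet and cognitive activity.

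The Discussion gives metformin's effect on such factors as a reason for choosing the drug: "It showed beneficial effects on several risk factors for dementia/AD, e.g. peripheral insulin resistance, T2D, metabolic syndrome, elevated adiposity, and cardiovascular factors".

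On the groups compared, Study design says that eligible participants in the active arm "will be randomised 1:1:1 to receive metformin 2000 mg/day, metformin 1000 mg/day, or placebo, together with the SMLI". On analysis, Statistics says that for most of these exploratory outcomes "the same model in the primary analysis of the trial will be used for continuous outcome variables". That model contains randomised group, time, their interaction, and site.

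**The concern.** The outcome mixes two kinds of variable. Exercise, diet and cognitive activity are things participants do. Body weight, waist, glucose, lipids and blood pressure are states that behaviour can change, but the document says the drug acts on factors of this kind too. If the drug lowers weight or glucose and nobody changes behaviour, the outcome still differs between groups. Under the abstract's wording, that difference counts as interaction.

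This matters because of how the results will be used. Limitations says that evidence on metformin-lifestyle interactions is sparse and that it is unclear which dose gives most benefit in combination with lifestyle change. It then says that the findings will inform dose selection and design for phase III. Objective (i) is the part of the trial aimed at interaction. An ordinary pharmacological response, reported under its label, could be taken into that planning as a sign that drug and lifestyle reinforce each other.

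**Working it through.** **Step 1: what the planned comparison estimates.** Write m = 1 for metformin and 0 for placebo, and s = 1 for SMLI and 0 for none. For a cardiometabolic factor Y, let

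E[Y] = μ + αm + βs + γms,

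where α is the drug effect without the SMLI and γ is the factorial interaction. Every participant in the trial-within-trial has s = 1 (Study design). The metformin-placebo difference is therefore

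(μ + α + β + γ) − (μ + β) = α + γ.

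Only the sum is estimable. To separate γ from α, one needs metformin with s = 0, and no group has that. The group-by-time term in the model does not help, because it is the same contrast expressed as change over time.

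**Step 2: whether it shows a lifestyle change.** Within s = 1, split the difference in Y into a direct drug part δ and a part that runs through behaviour, κΔB. Here ΔB is the metformin-placebo difference in behaviour and κ is the effect of behaviour on Y:

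difference in Y = δ + κΔB.

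The Discussion implies that δ is not zero for these factors. A non-zero difference is therefore compatible with ΔB = 0. For a directly measured behaviour (activity, diet, cognitive activity), the difference is ΔB itself, so it can be read as metformin altering lifestyle uptake. The problem is confined to the cardiometabolic and biomarker components.

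**Step 3: an illustration of size.** The document gives no sample-size or power figure for this comparison, so there is nothing to reproduce. Its one sample-size calculation, 506 evaluable participants for the main comparison, does not bear on the point.

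Inputs:
- SMLI recipients: about 300 (Metformin/placebo treatment).
- Share eligible for study drug: "estimated rate based on data from recruitment sources = 50%, unpublished". So 300 × 0.50 = 150, and 150 / 3 = 50 per group.
- Drop-out 15% (Statistics, main trial): 50 × 0.85 = 42.5 per group.
- Direct drug effect d, in SD units: not given; assumed range 0.2 to 0.5.
- Behaviour change and factorial interaction: both set to zero.
- Test: two-sample t, two-sided 5% (sidedness assumed), noncentrality d × √(n/2). For d = 0.3 and n = 50 this is 0.3 × 5 = 1.5.

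Chance of a significant difference, one dose against placebo:

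| Assumed d | 50 per group | 42.5 per group |
|---|---|---|
| 0.2 | 17% | 15% |
| 0.3 | 32% | 28% |
| 0.5 | 70% | 62% |

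A simulation of 20,000 trials with 50 per group gave 17%, 32% and 69%. In the same simulation, a true 2×2 interaction contrast with 50 in each of four groups stayed at about 5% for every d, as it should when γ = 0. That contrast needs the group that the trial lacks.

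**The case against.** The strongest reply is that this is a matter of labels. Management of cardiovascular and metabolic risk is itself one of the five SMLI components, so listing those factors follows the programme's own domains. How they respond by dose group on a common SMLI background is useful to know. The outcome is exploratory, the list is only illustrative, and the underlying measures are collected one by one. Uptake of the programme is covered separately by the adherence outcome. Limitations already disclaims efficacy data on metformin's added benefit.

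Most of this stands, and it limits the point. It is a reason to keep the cardiometabolic factors as an outcome. It does not justify calling a difference in them an interaction, and the abstract does so explicitly. The disclaimer in Limitations concerns efficacy over lifestyle alone. It does not warn that drug effect and lifestyle change are mixed in this outcome. Nor is this detail left to an analysis plan, because the article itself fixes both the grouping and the reading.

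Two stronger readings should not be drawn:

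- **Masking.** A reader might infer that drug-induced weight loss could hide reduced exercise in a metformin group. That would need the components to be summed, and no composite is planned for these groups. The Healthy Lifestyle Index does include cardiovascular risk factors, but it is a secondary outcome, assigned to the FINGER 2.0 versus SGMI comparison.
- **Inflated false-positive rate.** A reader might take the percentages in the table as error rates that ought to be 5%. They are ordinary power to detect a real drug effect of an assumed size. What goes wrong is the interpretation of a true difference.

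**Conclusion.** The point holds for the cardiometabolic factors and related biomarkers in exploratory outcome (i). A metformin-placebo difference there is the drug effect given SMLI and cannot by itself show a lifestyle change or an interaction. This follows from the article's own statements and from the absence of a metformin group not receiving the SMLI. It needs no assumption about effect size. The 15% to 70% range is illustrative only: it rests on an assumed drug effect of 0.2 to 0.5 SD, on the projected 50% eligibility, and on either full retention or the main trial's 15% drop-out.

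A reader might infer that the whole of outcome (i), or the trial's main result, is compromised. The documents do not support that. Differences in exercise, diet or cognitive activity remain interpretable as effects on lifestyle uptake, and the primary and secondary comparisons of FINGER 2.0 with SGMI are not affected. The change is worth making because it decides what objective (i) can conclude, and it costs little.

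**What to change.** 1. In exploratory outcome (i), the Table 2 row and the abstract phrase, limit the healthy-lifestyle label to behavioural measures already collected: diet, physical activity (self-reported and Actigraph) and cognitive activity. Read SMLI adherence, already in outcome (iii), alongside them.
2. Keep the cardiometabolic factors and biomarkers as a separately labelled exploratory outcome: drug-responsive risk factors by dose group, on a common SMLI background.
3. State that a behavioural difference shows whether metformin alters lifestyle uptake. Add that diet may also shift through gastrointestinal side effects, which the Metformin/placebo treatment section names as the most common adverse events, so a dietary difference needs cautious reading.
4. State that a factorial metformin-by-lifestyle interaction cannot be estimated without a metformin group not receiving the SMLI, and word objective (i) to match.

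The cost is rewording in a few places. No new data, visits or participants are needed. The downside is a smaller set of lifestyle outcomes and a narrower stated objective.
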